### Objectives

The current Standard Protocol Items: Recommendations for Interventional Trials (SPIRIT)-compliant [34] protocol outlines the methodology of a CONSORT-compliant [35] RCT, the primary objective of which is to establish the efficacy of the iCBT program for PTSD. Secondary objectives are to examine change in IU and emotion regulation ability following the iCBT program and the association between change in each of these constructs and PTSD symptom change following the PTSD program.

The proposed iCBT program aims to reduce psychological distress and PTSD symptoms in those with PTSD. It comprises psychoeducation about the trauma reaction and how it is maintained after the event by particular patterns of thinking, feeling and behaving. Dearousal skills are taught and practiced. Participants are taught ways to identify and change unhelpful thoughts about the trauma. They will be habituated to their challenging trauma memories using a series of brief structured writing assignments and taught graded exposure methods to re-enter feared situations. Finally, relapse prevention will cover continued skills practice and instruction on independent management of potential future setbacks. These elements have been incorporated into standard CBT-based treatment for PTSD both in internet and face-to-face formats [12, 18–21, 36–38], but have been adapted for the proposed internet treatment program.

Hypotheses are as follows: (1) patients receiving iCBT for PTSD will show greater mean symptom reduction on a standardised PTSD measure than a waitlist control group during treatment and at the end of treatment (the primary endpoint), with preserved symptom reduction at 3-month follow-up; (2) IU will be less at post-treatment than pre-treatment; (3) reduction in IU over treatment will be associated with reduction in PTSD severity; (4) emotion regulation will be greater at post-treatment than pre-treatment; and (5) increased emotion regulation after treatment will be associated with reduced PTSD severity after treatment.

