### Participants and recruitment

Participants will be recruited through flyers, paid print and internet advertising. Applicants will first complete online screening questionnaires about symptoms and demographic details (see Fig. 1 for a participant flow chart). Inclusion criteria are as follows: meet diagnostic criteria for PTSD; computer, internet and printer access; Australian resident; fluent in written and spoken English; willing to provide name, phone number and address, and to provide the name and address of a local general practitioner. Exclusion criteria are as follows: trauma occurrence within the past 4 weeks; non-resident of Australia; less than 18 years of age; currently receiving treatment for trauma/PTSD; frequent suicidal ideation (indicated by a score of 3 to item 9 of the Patient Health Questionnaire 9-item version (PHQ9)); regularly using illicit drugs or regularly consuming more than three standard drinks per day; psychotic disorder or taking atypical antipsychotics or benzodiazepines; if taking medication for anxiety or depression, has been taking the same dose for less than 1 month or intending to change the dose during the course of the program; currently highly dissociative (indicated by score ≥40 on the Dissociative Experiences Scale as per Spence et al. [20]); current or pending medicolegal proceedings associated with the reported trauma; applying for, or receiving, Workers Compensation associated with their trauma or PTSD. Excluded applicants will receive information on alternative services and will be encouraged to discuss their symptoms with their physician. Applicants who pass the screening phase will be telephoned for a diagnostic interview using the PTSD module from the Mini International Neuropsychiatric Interview version 5.0.0 (MINI) [39] to determine whether they meet diagnostic criteria for PTSD. All interviews will be conducted by a registered Clinical Psychologist (AA) or Clinical Trials Manager (JS) under the guidance of the Clinical Psychologist and trained in administration of the diagnostic interview. Applicants who satisfy all inclusion criteria will be informed of the study design and will complete an electronic informed consent prior to enrolling in the trial. Information from the diagnostic interview will be used for research purposes only for those participants who provide informed consent. All participants will be informed in writing that they may withdraw from the study (i.e. choose to cease program enrolment or choose for their data to be excluded from the RCT) at any time without jeopardising their relationship with St. Vincent’s Hospital or the University of New South Wales. Further, those participants randomised to the waitlist control group will be informed that should they commence a trauma-focused intervention outside of the trial, their data will be omitted from the RCT.

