### Participant monitoring

The Clinical Trials Manager of CRUfAD and a member of the research team will oversee participant monitoring. Symptom severity of the target disorder and general distress levels are measured before, during, and immediately upon completing the PTSD program based on empirically validated standardised internet-delivered symptom measures. Participants will be sent automated emails at the completion of each lesson to encourage skills practice. Patient queries throughout the program are primarily addressed by email contact from the clinician (AA) or the Clinical Trials Manager (JS). If clinically indicated, or if a patient’s K10 and/or PHQ9 or PCL-C scores deteriorate, the clinician makes telephone contact. If a participant misses a lesson, a member of the research team will send an email reminder (via the Virtual Clinic system) or will make telephone contact to remind the participant to complete the lesson.

The treatment group will be required to complete the iCBT program within 10 weeks to remain in the trial. Adherence is monitored throughout the program. Once enrolled, a participant can elect to discontinue at any time. A participant may be withdrawn from the trial (typically meaning course access will be closed) for the following reasons: lack of computer and internet access; change in prescribed medication for anxiety or depression; change in medication status of exclusion medications; suicidality or clinical risk; failure to complete baseline questionnaires; failure to commence the PTSD program. Lack of adherence throughout the iCBT program is not a specified reason for participant withdrawal, although a participant may withdraw voluntarily. Those in the waitlist control group will be required to complete questionnaires at weeks 1, 5 and 11 of the waitlist period to remain in the RCT. The waitlist control group will have access to the iCBT program immediately at the conclusion of the waitlist period. All reasons for withdrawal status will be documented.

To promote participant retention, participants are reminded that data collection is an important aspect of research and enables the research team to track their progress and to evaluate the program. Any adverse events will be reported to the Director of CRUfAD (GA) and to the Human Research Ethics Committee (HREC) of St Vincent’s Hospital, the responsible body for initiating a clinical trial audit.

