### Statistical methods

Power calculations were informed by calculation of effect size data from Spence et al. [20], providing a between-group effect corresponding to Hedges’ g of 0.47. The minimum sample size for each group (alpha set at 0.05, power at 0.80) was identified as 72, but at least 10 % more will be recruited to hedge against expected attrition. All analyses will be conducted at conclusion of the trial period (i.e. after all participants in the treatment group have completed the iCBT program). Significance testing of group differences regarding demographic data and pre-treatment measurements will be conducted using analysis of variance (ANOVA) and χ2 where the variables consist of nominal (or categorical) data. Intent-to-treat (ITT) mixed models using restricted maximum likelihood (REML) estimation will be used to account for missing data due to participant drop-out. Mixed models do not assume that the last measurement is stable (the last observation carried forward assumption) [63]. REML models are appropriate for RCTs with multiple time points and pre-to post-only designs [64]. The assumption that data are missing at random (MAR) will be evaluated using binary logistic regression to predict drop-out (0 = no drop-out, 1 = drop-out) and by comparing these two groups on baseline measures. Significant effects will be followed up with pairwise contrasts comparing mean pre-treatment to mean post-treatment scores. Complete-case analyses of the primary hypotheses using data from participants who complete all six lessons of the PTSD program will also be conducted. The effect of potential treatment moderators (e.g. time post-trauma, number of traumatic events) will be evaluated by including baseline variables of interest as a covariate and interaction term in separate mixed models analyses. Analyses will be performed in IBM SPSS version 21. Effect sizes will be calculated between groups (Hedges’ g) and within groups (Cohen’s d, adjusting for the repeated measures correlation) using the pooled standard deviation and adjusted for sample size.

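### The planned MAR check uses observed data only and cannot tell MAR from MNAR; the six-lesson analysis is an iCBT completer set with no defined waitlist comparator, not a complete-case analysis

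*Protocol article*

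**What the plan says.** All of the analysis text is in the protocol article, Statistical methods. The main analysis handles missing data through its likelihood: "Intent-to-treat (ITT) mixed models using restricted maximum likelihood (REML) estimation will be used to account for missing data due to participant drop-out". The assumption behind it is then to be checked: "The assumption that data are missing at random (MAR) will be evaluated using binary logistic regression to predict drop-out". A second part of the check sets drop-outs against non-drop-outs: "and by comparing these two groups on baseline measures". A further analysis follows: "Complete-case analyses of the primary hypotheses using data from participants who complete all six lessons of the PTSD program will also be conducted".

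Three other places bear on that further analysis. The primary hypothesis (Objectives) is a comparison between arms: iCBT patients "will show greater mean symptom reduction on a standardised PTSD measure than a waitlist control group during treatment and at the end of treatment". Under Participant monitoring, "The waitlist control group will have access to the iCBT program immediately at the conclusion of the waitlist period". The waitlist also has entry and exit rules of its own. Participant monitoring sets a condition for staying in the trial: "Those in the waitlist control group will be required to complete questionnaires at weeks 1, 5 and 11 of the waitlist period to remain in". Under Participants and recruitment, waitlist members are told that "should they commence a trauma-focused intervention outside of the trial, their data will be omitted from the RCT".

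**The concern.** There are two separate problems.

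First, the MAR check is given a job it cannot do. MAR concerns whether drop-out depends on the missing scores once the observed ones are taken into account. A regression of drop-out on observed variables never sees the missing scores. The mixed model relies on MAR, so a report could claim support for that assumption from a null regression, or doubt it because of a significant one. Neither conclusion would follow.

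Second, the analysis labelled complete-case is not defined by having complete outcome data. It is defined by adherence, which is observed after randomisation and, during the controlled phase, only in the iCBT arm. A comparison built on that set is no longer randomised. If it agreed with the intention-to-treat result, that agreement would not corroborate it.

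**Working it through.** **The plan's own figure.** n per group = 2(1.96 + 0.8416)² / 0.47² = 15.70 / 0.2209 = 71.1, so 72 (73 by the t distribution, where power at 72 is 0.7998). The stated 72 reproduces. Adding 10% gives 72 × 1.10 = 79.2. The point does not affect the sample size; the figure only sets the scale used below.

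**Why the check cannot work.** Write D for drop-out, X for observed data and Y for the missing post-treatment score. In general, logit P(D = 1) = α + βX + γY.

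- MCAR means β = 0 and γ = 0.
- MAR means γ = 0, with β free.
- MNAR means γ ≠ 0.

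The planned regression fits α + βX. It can reject β = 0, which counts against MCAR and is fully compatible with MAR. It cannot estimate γ, because Y is absent for everyone with D = 1. Comparing the two groups on baseline measures is the same test in another form.

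**Illustration of size.** All inputs are assumptions except the scale: 158 participants (79 per arm), 25% drop-out, two time points, baseline–post correlation 0.5, higher (worse) scores more likely to drop out, odds ratio 2 to 3 per SD (2 for the baseline row), and 1,500 simulated trials per scenario. A trial is flagged when baseline severity predicts drop-out at p < 0.05.

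| Drop-out depends on | MAR | Flagged | Bias in treatment difference |
|---|---|---|---|
| Baseline | holds | about 94% | none |
| The part of the outcome unrelated to baseline | fails | about 4–6% | see below |
| The outcome itself, iCBT arm only | fails | about 12–22% | see below |
| The outcome itself, both arms | fails | about 42–72% | about zero |

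Where MAR fails in one arm only, the bias in the treatment difference is about 0.12–0.20 SD over these mechanisms. Where the mechanism is the same in both arms, the two biases cancel. The direction depends on the arm: loss of the worst scores from iCBT overstates the effect, and the same loss from the waitlist understates it.

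The harmless case is flagged more often than any harmful one, so a flag does not indicate bias and its absence does not exclude it.

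A second set of assumptions gives the same pattern: 80 per arm, an interim visit, correlation 0.6, about 20–24% drop-out, log-odds slope 1 per SD, 2,000 trials. The flag rate is 5.8% under MCAR. It is 99.8% under baseline-dependent MAR (bias 0.007 SD). It is 4.6% when drop-out in iCBT depends on the outcome residual (bias 0.15 SD).

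**The six-lesson set.**

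- The hypothesis compares iCBT with waitlist, and the waitlist has no lessons until its waiting period ends. Before week 11 the filter can therefore remove people only from iCBT.
- Read literally, no waitlist member qualifies and there is no comparison. Read loosely, some waitlist set is used, but the article does not say which. The questionnaire and outside-treatment rules quoted above are filters of a different kind from lesson completion.
- Participant monitoring says poor adherence is not a specified reason for withdrawal, so iCBT participants with outcome data but fewer than six lessons can exist and would be excluded. A true complete-case set would keep them. The same section also makes finishing within 10 weeks a condition of staying in the trial, so how many such people there will be is unclear.

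**The case against.** **What stands against the point.** The primary analysis is intention-to-treat by a mixed model, and nothing here shows that model to be wrong. The illustration is sensitive to its inputs. The very low flag rates arise only when drop-out depends on the part of the outcome that baseline does not predict; if it depends on the outcome itself, baseline acts as a proxy and the check fires more often. Bias in the treatment difference needs a mechanism that differs between arms. The article gives no drop-out rate beyond the 10% allowance. The two-time-point illustration also ignores the PCL-C taken before each lesson and at week 5, which the mixed model can use. A journal article may properly leave MNAR sensitivity analyses to a fuller plan, so their absence is not the finding.

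None of this rescues the sentence on MAR. It assigns a purpose to a named procedure, and the procedure cannot serve it under any choice of inputs.

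**Stronger readings that the documents do not support.**

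- A reader might infer that the six-lesson analysis is a second planned drop-out check. The article presents it only as an additional analysis of the primary hypotheses.
- A reader might infer that iCBT completers will be compared with every randomised waitlist member. That is a natural reading, but it is not stated.
- A reader might set the bias against the planning effect of 0.47 and conclude that a fixed share of it is spurious. That requires MNAR in one arm only, at assumed strengths, and the documents say nothing on either.
- A reader might expect the team to abandon a valid model after a significant regression. The article gives no rule for acting on the result.

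**Conclusion.** The point holds as two limited corrections. The check described for MAR cannot evaluate MAR. That follows from the definitions and needs no assumed numbers. The illustration adds only scale: about 94% flagged with no bias when MAR holds, against about 4–72% when it fails, with a bias in the treatment difference between about zero and 0.20 SD depending on whether the mechanism acts in both arms or one. Those figures rest on the assumed drop-out rate, correlation and odds ratios.

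The six-lesson analysis is a completer (per-protocol) set under the wrong name, selected after randomisation within iCBT, with its waitlist comparator undefined. The size of any distortion cannot be given from the documents, because neither the comparator nor the prognosis of non-completers is stated. The primary intention-to-treat estimate does not depend on it. Both corrections should be made before analysis, mainly to prevent unsupported statements in the report.

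**What to change.** 1. Describe the logistic regression and the baseline comparison as exploring predictors of drop-out, and remove the statement that they evaluate MAR. Include the predictors found in a sensitivity version of the mixed model, since MAR is more plausible given those variables.
2. Assess robustness to MAR with a delta-adjusted (tipping-point) analysis of post-treatment PCL-C (week 11 on the waitlist). Shift the imputed scores of drop-outs in steps, vary the shift separately by arm, and report where the conclusion changes. Varying it by arm matters because equal shifts largely cancel when drop-out is similar in the two arms.
3. Relabel the six-lesson analysis as per-protocol or completer, state which waitlist participants enter it, present it as non-randomised and descriptive, and do not cite it as support for the intention-to-treat result. If a complete-case analysis is wanted, define it by available outcome data in both arms.

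A complier-average effect defined by finishing six lessons is not a good substitute. It would require that fewer than six lessons have no effect, whereas Table 2 places controlled breathing, the trauma narrative, thought challenging and situational exposure in lessons 2 to 5.

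The cost is some rewording and a little extra analysis, with no new data and no change in sample size.

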Mediation analyses will be used to examine the association between change in PTSD symptoms over treatment and change in each of IU and emotion regulation in separate analyses. Tests of the indirect effects (mediation) will be conducted using PROCESS [65]. This method was chosen over the causal steps approach [66] based on recent research advocating the use of modern statistical approaches to quantify intervening variable models [67]. As recommended, particularly for small samples, estimates of indirect effects will be generated using bootstrapping analysis see [68, 69]. Bootstrapping is a nonparametric resampling method that generates an estimate of the indirect effect, and does not require assumptions about the shape of the sampling distribution that underlie the Sobel test. In bootstrapping analysis, the most stringent test of an indirect effect (mediation) is if the 95 % bias corrected and accelerated confidence intervals for the indirect effect do not include the value of 0. When zero is outside of the 95 % confidence interval estimate, the indirect effect is declared statistically different from zero at *p* < 0.05 (two-tailed), indicating that the effect of the independent variable on the dependent variable is contingent upon the effect of the proposed mediator [68]. In the current study, PROCESS for SPSS will be used to estimate 5000 bias-corrected bootstrap 95 % confidence intervals.

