## Discussion

The current RCT will test the efficacy of an iCBT intervention for PTSD. It seeks to replicate previous efficacy findings [20, 23] of iCBT for PTSD in a formally assessed PTSD sample from the general population. Moreover, it will examine the relationship between PTSD symptom change following treatment and changes in IU and emotion regulation. As such, results from the proposed RCT may point to future lines of enquiry into the role of these constructs in the mechanism of PTSD symptom change during CBT.

Notwithstanding the potential utility of the proposed RCT, the following potential limitations are noted. The control group in the current study is a waitlist control, rather than an active treatment control. Therefore, it will not be possible to eliminate a potential placebo effect. Moreover, the results will not speak to the relative utility of iCBT for PTSD compared to an alternative treatment approach or modality. These will be questions for future research. Further, while the trial will examine potential change in IU and emotion regulation ability, the iCBT program was not written to specifically target either of these constructs. As such, results will not permit definitive conclusions as to how treatment components impact these constructs. The current RCT will use DSM-IV PTSD diagnostic criteria and associated standardised assessment instruments, as validated DSM-5 measures were not available when recruitment began for the current project. While items reflecting the three additional DSM-5 PTSD symptoms from the PCL-5 have been included, it is important to note that formal diagnostic and associated self-report measures do not measure DSM-5 PTSD criteria specifically. We note that while having different clinicians conduct pre-treatment and follow-up interviews controls for bias, it may introduce inter-rater variability.

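### Hypotheses 3 and 5 state an association, but the only decision rule given is for the indirect effect, which can miss a strong association if iCBT moves the mediator little relative to waitlist

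*Protocol article*

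**What the plan says.** In Objectives, the protocol article separates two kinds of secondary question. Hypotheses 2 and 4 predict that IU falls and emotion regulation rises from pre- to post-treatment. Hypotheses 3 and 5 are about association: "reduction in IU over treatment will be associated with reduction in PTSD severity" and "increased emotion regulation after treatment will be associated with reduced PTSD severity after treatment".

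Statistical methods gives one analysis for the association: "Mediation analyses will be used to examine the association between change in PTSD symptoms over treatment and change in each of IU" and emotion regulation, separately. It continues: "Tests of the indirect effects (mediation) will be conducted using PROCESS". The criterion is that the 95% "confidence intervals for the indirect effect do not include the value of 0", and the consequence is stated: "When zero is outside of the 95 % confidence interval estimate, the indirect effect is declared statistically different from zero". The computational setting is "PROCESS for SPSS will be used to estimate 5000 bias-corrected bootstrap 95 % confidence intervals". No criterion is attached to the mediator–outcome slope or to a correlation of changes, and the independent variable of the mediation model is not named.

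Two other places bear on the point. The Background gives mediators of symptom change as something the trial will examine. The Discussion notes that "the iCBT program was not written to specifically target either of these constructs".

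**The concern.** The null hypothesis behind hypotheses 3 and 5 is that mediator change and PCL-C change are unrelated (b = 0). The null behind the stated rule is a×b = 0, which is also true when b is large and a = 0. An interval that includes zero therefore has two possible explanations: no association, or too little effect of iCBT on the mediator relative to waitlist. The plan gives no rule for telling them apart.

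At stake are two of the five stated hypotheses, both secondary. If the slope is clearly non-zero but the indirect-effect interval includes zero, the plan gives no basis for calling the association supported, and turning to the slope at that point would be a post hoc choice. The primary comparison on the PCL-C is not affected.

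**Working it through.** **Inputs from the document.** 72 per arm as the minimum sample size, alpha 0.05, power 0.80, Hedges' g 0.47 (Statistical methods); 1:1 allocation (Trial design and blinding); 5000 bias-corrected bootstrap resamples.

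**Inputs not in the document, so assumed.** The effect a of iCBT versus waitlist on mediator change, in SD units: 0 to 0.8. The within-arm correlation r between mediator change and PCL-C change: 0.3 to 0.5. Also assumed: randomised arm is the independent variable, errors are normal, data are complete, and the slope is the same in both arms.

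**The plan's own figure.** n per arm = 2 × (1.960 + 0.842)² / 0.47² = 2 × 7.85 / 0.2209 = 71.1, rounded up to 72. The t-test version gives 72.04, with power 0.7998 at 72. The sample size reproduces and is not in dispute.

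**Approximate arithmetic.** The indirect effect is found roughly when both paths are significant.

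- Path a: SE = √(2/72) = 0.167, so z = a/0.167. At a = 0.2, z = 1.20 and power is about Φ(1.20 − 1.96) = 0.22. At a = 0.3, z = 1.80 and power is about Φ(−0.16) = 0.44. At a = 0.47, z = 2.82 and power is about Φ(0.86) = 0.81.
- Path b, adjusted for arm: t ≈ r√(144 − 3)/√(1 − r²). At r = 0.3, t = 0.3 × 11.87/0.954 = 3.73 and power is about Φ(1.77) = 0.96. At r = 0.5, t = 0.5 × 11.87/0.866 = 6.86 and power is about 1.00.

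Path b is well powered throughout and does not depend on a. Path a is therefore what limits the indirect-effect test. Path a reaches 50% power at a = 1.96 × 0.167 = 0.33.

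**Simulation.** 72 per arm, 600 trials per cell, 800 resamples; simulation error at most about ±0.04.

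| a | Indirect, bias-corrected, r = 0.3 / 0.5 | Indirect, percentile, r = 0.3 / 0.5 | Direct slope test, r = 0.3 / 0.5 |
|---|---|---|---|
| 0 | 0.09 / 0.07 | 0.05 / 0.06 | 0.95 / 1.00 |
| 0.1 | 0.13 / 0.12 | 0.10 / 0.10 | 0.95 / 1.00 |
| 0.2 | 0.29 / 0.27 | 0.23 / 0.24 | 0.97 / 1.00 |
| 0.3 | 0.50 / 0.48 | 0.44 / 0.45 | 0.96 / 1.00 |
| 0.47 | 0.82 / 0.81 | 0.75 / 0.79 | 0.95 / 1.00 |
| 0.6 | 0.92 / 0.95 | 0.89 / 0.95 | 0.96 / 1.00 |
| 0.8 | 0.98 / 1.00 | 0.96 / 1.00 | 0.96 / 1.00 |

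A second simulation with the planned 5000 resamples and 1000 trials per cell agrees. At r = 0.4 the bias-corrected rule detects the association in 6%, 11%, 28%, 49% and 83% of trials at a = 0, 0.1, 0.2, 0.3 and 0.47, against more than 99% for the direct test. At r = 0.3 the direct test reaches 94–96%.

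The bias-corrected rate at a = 0 is only the rule's false-positive rate for mediation. It is not real sensitivity to the association.

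**The case against.** The strongest reply is that mediation is a stated aim. The Background says that the two earlier trials in formally diagnosed samples did not examine mediators and that this one will, and an indirect-effect test is suited to that. This stands, so the test should be kept. It does not settle hypotheses 3 and 5, which are worded as associations and listed apart from the predictions that the mediators change.

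A reader might infer that a true association would usually be missed. The documents do not support that without a condition. They give no effect on either mediator. The remark in the Discussion that the program was not aimed at these constructs does not predict a small change. The Background links psychological treatment to lower IU and exposure-based PTSD treatment to better emotion regulation, and hypotheses 2 and 4 predict change in both. If a were as large as the trial's planning effect of 0.47, the rule would succeed in about four trials in five.

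A reader might also infer that hypotheses 3 and 5 would fail simply because hypotheses 2 and 4 had failed. That does not follow. Hypotheses 2 and 4 are pre-to-post comparisons, whereas a is a between-arm contrast. IU could fall in both arms, supporting hypothesis 2, while a is zero.

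Three further points stand in part. PROCESS estimates the slope anyway, but the plan attaches no conclusion to it. The plan does not say that an interval including zero refutes the association, but it gives no other route to supporting it. The error is one-directional: a non-zero a×b requires a non-zero b, so the risk is missed associations rather than spurious ones.

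That a fuller protocol or analysis plan may exist is not an answer. The article does state a rule for this question, and the rule answers a different one.

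**Conclusion.** The point holds in conditional form. The stated rule tests mediation, while hypotheses 3 and 5 state association, and the two part company when iCBT has little effect on the mediator relative to waitlist. With 72 per arm and r = 0.3 to 0.5, the association is missed more often than not only if a is below about 0.3. At a = 0.47 the loss against a direct test is roughly 13 to 19 percentage points (0.95 − 0.82 at r = 0.3; 1.00 − 0.81 at r = 0.5). By a = 0.8 it has essentially gone.

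These sizes rest on assumed values of a and r and on randomised arm as the independent variable. How often the association would be missed in this trial cannot be read from the documents. It would also go too far to call the indirect-effect test wrong for the trial: it fits the mediation aim, and it is only the sole criterion for two hypotheses that ask something else. The change is worth making because it is nearly free.

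**What to change.** In Statistical methods:

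- Name randomised arm as the independent variable of the mediation model, if that is what is intended.
- Test hypotheses 3 and 5 by the slope of PCL-C change on mediator change, adjusted for arm, with its 95% confidence interval.
- Keep the bootstrap interval for the indirect effect as a separate test of the mediation aim in the Background.
- State that an indirect-effect interval including zero does not by itself refute hypothesis 3 or 5.

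The cost is wording. The slope is already in the PROCESS output, so no new data or model is needed. The downside is one more reported test per mediator scale, or more if reappraisal and suppression on the Emotion Regulation Questionnaire are analysed separately.
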